## Abstract

**Background:**

Ultrasound accelerates thrombolysis with tPA (sonothrombolysis). Ultrasound in the absence of tPA also accelerates clot break-up (sonolysis). Adding intravenous gaseous microbubbles may potentiate the effect of ultrasound in both sonothrombolysis and sonolysis. The Norwegian Sonothrombolysis in Acute Stroke Study aims in a pragmatic approach to assess the effect and safety of contrast enhanced ultrasound treatment in unselected acute ischaemic stroke patients.

**Methods/Design:**

Acute ischaemic stroke patients ≥18 years, with or without visible arterial occlusion on computed tomography angiography (CTA) and treatable ≤ 4½ hours after symptom onset, are included in NOR-SASS. NOR-SASS is superimposed on a separate trial randomising patients with acute ischemic stroke to either tenecteplase or alteplase (The Norwegian Tenecteplase Stroke Trial NOR-TEST). The NOR-SASS trial has two arms: 1) the thrombolysis-arms (NOR-SASS A and B) includes patients given intravenous thrombolysis (tenecteplase or alteplase), and 2) the no-thrombolysis-arm (NOR-SASS C) includes patients with contraindications to thrombolysis. First step randomisation of NOR-SASS A is embedded in NOR-TEST as a 1:1 randomisation to either tenecteplase or alteplase. Second step NOR-SASS randomisation is 1:1 to either contrast enhanced sonothrombolysis (CEST) or sham CEST. Randomisation in NOR-SASS B (routine alteplase group) is 1:1 to either CEST or sham CEST. Randomisation of NOR-SASS C is 1:1 to either contrast enhanced sonolysis (CES) or sham CES. Ultrasound is given for one hour using a 2-MHz pulsed-wave diagnostic ultrasound probe. Microbubble contrast (SonoVue®) is given as a continuous infusion for ~30 min. Recanalisation is assessed at 60 min after start of CEST/CES. Magnetic resonance imaging and angiography is performed after 24 h of stroke onset. Primary study endpoints are 1) major neurological improvement measured with NIHSS score at 24 h and 2) favourable functional outcome defined as mRS 0–1 at 90 days.

**Discussion:**

NOR-SASS is the first randomised controlled trial designed to test the superiority of contrast enhanced ultrasound treatment given ≤4½ hours after stroke onset in an unselected acute ischaemic stroke population eligible or not eligible for intravenous thrombolysis, with or without a defined arterial occlusion on CTA. If a positive effect and safety can be proven, contrast enhanced ultrasound treatment will be an option for all acute ischaemic stroke patients. EudraCT No 201200032341; www.clinicaltrials.gov NCT01949961.

## Background

The common denominator of acute ischaemic stroke is a thromboembolic arterial occlusion. Intravenous (iv) thrombolysis with recombinant tissue plasminogen activator (tPA) is the only proven effective treatment for achieving arterial recanalisation and does improve outcome if given within 4½ hours from symptom onset [1]. However, recanalisation is achieved in only 30-40 % of patients who undergo thrombolysis [2]. As a result, many patients are left with a substantial brain damage, with high rates of disability and mortality [3].

Transcranial ultrasound has been shown in vitro and in vivo to accelerate thrombolysis [4–6] Ultrasound energy promotes motion of fluid around the thrombus (microstreaming) [7], stimulates arterial dilation, weakens fibrin cross-links, increases uptake and penetration of tPA and increases tPA concentration within the thrombus [8–11]. Ultrasound may thus promote tPA delivery despite stagnant flow near the occlusion.

In animal studies, ultrasound with frequencies from 27 kHz to 200 kHz increases the thrombolytic effect of iv thrombolysis [12]. However, low-frequency transcranial ultrasound (<1 MHz) carries an increased risk of opening the blood–brain barrier (BBB) [13, 14] and is also associated with productions of undesired standing waves and cavitation in the brain [15]. Both opening of the BBB and occurrence of standing waves during low frequency ultrasound insonation may therefore increase intracerebral bleedings when combined with iv thrombolysis [16, 17]. These results play an important role in designing a safer application of transcranial ultrasound in the brain [15].

In humans, ultrasound waves with a frequency of 2 MHz augment clot lysis [18] and recanalization when combined with iv thrombolysis (sonothrombolysis). Sonothrombolysis with pulsed-wave 2 MHz ultrasound is not associated with an increased risk of symptomatic intracerebral haemorrhage [19, 20], but is associated with a nearly 3-fold increased likelihood of complete recanalization and a 2-fold increased likelihood of functional independence at 3 months [19]. But even 2 MHz transcranial ultrasound with iv tPA has been shown to possibly increase the risk of symptomatic bleedings (TUCSON) [21, 22]. In particular low frequency (300 KHz) ultrasound seems to increase the risk of cerebral bleedings (TRUMBI) [16]. One randomised study with transcranial color-coded sonography (TCCS) using a 1.8-MHz Doppler ultrasound probe showed a beneficial effect on recanalisation and short term outcome in patients with middle cerebral artery main stem occlusion (MCA-M1), but with a tendency toward more severe haemorrhagic transformations in the ultrasound group [23]. At present, pulsed-wave 2 MHz ultrasound seems to be the safest approach for sonothrombolysis.

Adding gaseous microbubbles may increase the clot lysis with and without iv tPA both in vitro and in vivo [24]. Microbubbles potentiate the effect of ultrasound [25–27]. When exposed to ultrasound, microbubbles oscillate, expand or collapse producing stable cavitation (sustained bubble activity), which agitates the surrounding fluid, produces fluid jets that erode the thrombus surface, increases the surface area for thrombolytic action and accelerates lysis of clots [28–31]. Stable cavitation is associated with increased treatment effect [32], whereas inertial cavitation leads to microbubble destruction and decreases ultrasound mediated enhancement of sonothrombolysis [33]. The effect of ultrasound in sonothrombolysis and sonolysis are mainly influenced by three factors [24]: 1) the size of microbubbles which influences their resonant frequency [33]; 2) the increasing attenuation with increasing frequency which limits the depth of treatment at higher frequencies and 3) the increased risk of standing waves in the cerebral cavity at lower frequencies [34]. The use of lower ultrasound frequencies has the advantage of improving skull penetration and position tolerance due to insonation of a larger volume [24], but may increase the incidence of intracranial bleedings [16]. Higher ultrasound frequency (2 MHz) is therefore used in a clinical diagnostic setting. Adding microbubbles, i.e., iv ultrasound contrast, may induce further acceleration of ultrasound enhanced thrombolysis in acute ischaemic stroke patients, leading to a more complete recanalisation and better clinical outcome [4].

Contrast enhanced ultrasound insonation of thrombi in the absence of iv tPA has achieved high rates of recanalisation in animal models [35]. Repeated oscillations of the microbubbles around the clot cause an increase in local temperature due to the absorption of the energy from the radiated sound field and create further heating through viscous friction in the blood [36]. Microbubbles also penetrate the clot and make the tunnels in the fibrin matrix [24]. Experimental evidence thus indicates that ultrasound as such can accelerate clot break-up and lysis, both through mechanical (acoustic cavitation) and enzymatic mechanisms [28].

A high proportion of acute ischaemic patients are ineligible for iv tPA. The effect of ultrasound on the thrombus in the absence of tPA (sonolysis) is clinically not well studied, but transcranial 2 MHz ultrasound may have a lytic effect on the thrombus also without administration of tPA [22, 37–39]. This ultrasound effect is enhanced by echo contrast [31]. The same mechanisms as in the experimental studies may apply in humans, although the temperature effect may be negligible due to the ultrasound attenuation through the skull and tissue. It is nevertheless conceivable that contrast enhanced sonolysis (CES) may be more effective than ultrasound alone and may even have a neuroprotective role in acute ischaemic stroke patients [37, 40, 41]. Previous sonothrombolysis studies have focused on the subset of stroke patients eligible for thrombolysis. A number of patients have contraindications to thrombolysis and are left without a therapeutic option. No previous studies have systematically studied the effect of ultrasound in a general stroke population not eligible for iv thrombolysis. These subsets of patients are in desperate need of a treatment. NOR-SASS aims at testing a therapeutic option for these patients.

Alteplase has been used in previous sonothrombolysis studies. A growing body of evidence indicates that alteplase has a negative effect on the ischemic brain, including cytotoxicity and increased permeability of the blood brain barrier facilitating cerebral oedema [42]. An alternative thrombolytic therapy that might be easier and safer to administer could lead to wider acceptance and use of thrombolytic therapy [43] . Tenecteplase may be the drug of choice [44]. Tenecteplase is a modified tissue plasminogen activator that is more fibrin-specific, more resistant to plasminogen activator inhibitor (PAI), has a higher thrombolytic potency, with a longer half-life than alteplase and can therefore be administered as an intravenous bolus [43, 45]. No prior studies have investigated the combination of tenecteplase with contrast enhanced sonothrombolysis. NOR-SASS aims at testing the safety of tenecteplase in combination with contrast enhanced sonothrombolysis.

Previous sonothrombolysis studies were conducted in patients with an identified thrombus in major intracranial arteries [19, 46]. No previous studies have looked into the effect of ultrasound in minor stroke in the absence of a visible thrombus in the major intracranial arteries. Recanalisation rate following iv thrombolysis is higher with smaller thrombi in distal arteries [47]. It is therefore conceivable that ultrasound has even better effect on small, not visible peripheral arterial thrombi, on perforator thrombotic occlusions, or even thrombi in the microcirculation [35]. Several areas of peripheral vessels are, however, not accessible by ultrasound. Standard approaches never the less allow insonation of most of the clinically very relevant MCA-M3/M4, parts of the anterior and posterior cerebral vascular bed (transtemporal window) and the brainstem arteries (transforaminal window). Directing the ultrasound beam accurately onto hypothetical small peripheral occlusions includes a large degree of uncertainty, but a slight “fanning” movement of the probe increases the probability of covering the relevant region of interest.

Given the limited effect of iv thrombolysis and the logistic challenges in endovascular treatment, new therapeutic approaches for patients with acute ischaemic stroke are imperative. This protocol defines a pragmatic framework for routine ultrasound treatment in acute ischaemic stroke.

### Hypothesis

We hypothesise that in patients with acute ischaemic stroke eligible for intravenous thrombolysis, the clinical effect of contrast enhanced sonothrombolysis (CEST), given within 4½ hours from symptom onset is superior to that of intravenous thrombolysis alone. CEST is safe and effective in both proximal and distal thrombus, and may achieve higher recanalisation rates and better clinical outcome than intravenous thrombolysis alone.

We further hypothesise that in patients with acute ischaemic stroke not eligible for intravenous thrombolysis, the clinical effect of contrast enhanced sonolysis (CES) given within 4½ hours from symptom onset is superior to that of no specific treatment. CES is safe and effective in both proximal and distal thrombus, and may achieve higher recanalisation rates and better clinical outcome than no specific treatment.

### Aims of the study

The aims are to assess recanalisation, safety and clinical outcome of 1) CEST versus sham CEST in patients eligible for intravenous thrombolysis (NOR-SASS A and B) and 2) CES versus sham CES in patients not eligible for intravenous thrombolysis (NOR-SASS C).

## Design and methods

NOR-SASS is a multi-centre PROBE (prospective randomised open-label blinded endpoint) trial, designed to establish the superiority of contrast enhanced ultrasound treatment versus sham ultrasound treatment in consecutively admitted patients with acute ischaemic stroke. NOR-SASS is superimposed on a trial randomising patients with acute ischemic stroke to either tenecteplase or alteplase (The Norwegian Tenecteplase Stroke Trial; NOR-TEST; ClinicalTrials.gov NCT 01949948). NOR-SASS A includes patients willing to be randomised to either tenecteplase or alteplase in NOR-TEST, NOR-SASS B includes patients who did not give consent to be randomised and thus receive routine alteplase, and NOR-SASS C includes patients not eligible for iv thrombolysis.

NOR-SASS compares 1) ultrasound + microbubbles + randomised alteplase/tenecteplase versus sham ultrasound + sham microbubbles (plain saline) + alteplase/tenecteplase (NOR-SASS A) or 2) ultrasound + microbubbles + non-randomised routine alteplase versus sham ultrasound + sham microbubbles + alteplase (NOR-SASS B) and 3) ultrasound + microbubbles versus sham ultrasound + sham microbubbles (NOR-SASS C).

NOR-SASS A includes a first step randomisation 1:1 to either tenecteplase or alteplase and a second step randomisation 1:1 to either CEST or sham CEST. NOR-SASS B (alteplase group) randomisation is 1:1 to either CEST or sham CEST. NOR-SASS C randomisation is 1:1 to either CES or sham CES (Fig. 1).

**Fig. 1 Fig1:**
[figure not shown]
Randomization and flowchart. CEST Contrast enhanced sonothrombolysis with thrombolytic agent. CES Contrast enhanced sonolysis without thrombolytic agent

### Power calculation

Our NORSTROKE data base from before the initiation of the present study shows that patients treated with thrombolysis (n = 223) had a 37 % improvement of mean NIHSS from 8.7 to 5.5 (3.2; SD = 5.9) from admission to day 7. Based also on thrombolysis series in mild stroke and on a meta-analysis of sonothrombolysis studies [48], NOR-SASS aims at detecting a 15 % higher reduction of mean NIHSS among patients receiving sonothrombolysis vs. thrombolysis alone (p_1_ = 0.37; p_2_ = 0.52, power 0.8) and will include 276 patients over 3–4 years. The study was initiated at Haukeland University Hospital, Bergen, in Q3 2012 and is planned to close Q4 2016. An interim analysis is planned for Q2 2015. Per January 2014, 176 patients are enrolled.

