### Study endpoints

Primary study endpoints are 1) neurological improvement (NIHSS score) at 24 h (clinical effect; proof of concept) and 2) functional handicap defined as modified Rankin Scale (mRS) score 0–1 at 90 days (clinical outcome). Secondary study endpoints are 1) haemorrhagic transformation (haemorrhagic infarct/haematoma), 2) symptomatic cerebral haemorrhage (safety endpoint), 3) recanalisation at 2 h (optional), 4) recanalisation at 24–36 h, 5) MR-DWI lesion volume at 24–36 h and 6) death.

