### Statistical analysis

Statistical design is made in co-operation with the Centre for Clinical Research, Haukeland University Hospital. An interim analysis will be performed in Q2 2015. The exact method of the final analysis will be specified in the Statistical Analysis Plan, which will be drawn up prior to the closure of the database and the statistical analysis. The primary analysis is an “intention to treat” analysis. The results will also be tested in a “per protocol” analysis. Stratification according to age (≤80 versus >80), baseline NIHSS (≤14 versus >14), time (0–3 h vs. 3-4½ h), occlusion/no occlusion; correct/incorrect insonation focus (patients with no visible occlusion on CTA); atrial fibrillation/no atrial fibrillation will be performed. An analysis excluding MCA_1_ occlusion and MCA_1_- MCA_2_ occlusions will also be performed. Temporal bone window thickness will be included in the analysis. Serious Adverse Events (SAE) and Adverse Events (AE) will be analysed as appropriate.

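### The stated power of 0.8 comes from a change in mean NIHSS to day 7 under thrombolysis; it is not linked to either primary endpoint and does not cover the NOR-SASS C hypothesis

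*Protocol article*

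**What the plan says.** The Power calculation section starts from 223 thrombolysed patients in the NORSTROKE database, with a 37 % "improvement of mean NIHSS from 8.7 to 5.5 (3.2; SD = 5.9) from admission to day 7". It also refers to thrombolysis series in mild stroke and to a meta-analysis of sonothrombolysis studies, without giving figures from them. The target follows: "NOR-SASS aims at detecting a 15 % higher reduction of mean NIHSS among patients receiving sonothrombolysis vs. thrombolysis alone", entered as "p_1_ = 0.37; p_2_ = 0.52, power 0.8". The trial "will include 276 patients over 3–4 years". Neither alpha nor sidedness is given, and the target sentence carries no time point.

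The Study endpoints section reads: "Primary study endpoints are 1) neurological improvement (NIHSS score) at 24 h", with mRS 0–1 at 90 days as the second primary endpoint. Under Outcomes measures, neurological improvement at 24 h is a yes/no outcome: NIHSS 0, or a drop of at least 4 points from baseline. NIHSS at day 7 is scheduled in Table 2 but is neither a primary nor a secondary endpoint. The day-7 outcome under Outcomes measures is based on mRS.

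The Hypothesis section makes a separate claim for patients who cannot have thrombolysis: "the clinical effect of contrast enhanced sonolysis (CES) given within 4½ hours from symptom onset is superior to that of no specific treatment". Design and methods gives these patients (NOR-SASS C) their own 1:1 randomisation.

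**The concern.** A power statement tells the reader how likely the trial is to detect a named effect on the outcome that will be tested. Here the effect is built from one outcome and the trial will test two others. A relative fall in mean NIHSS over a week is not a 24-hour responder rate, and it carries no information about the proportion with mRS 0–1 at three months. The comparison named in the calculation is sonothrombolysis against thrombolysis alone, which leaves out NOR-SASS C.

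What is at stake is interpretation. Readers may credit 80 % power to the mRS 0–1 comparison or to the sonolysis comparison and take a null result as evidence of no effect, although the document supports that power for neither.

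**Working it through.** **1. What the 37 % is.** From the Power calculation section: 3.2/8.7 = 0.368. This is the fall in the mean divided by the baseline mean, and not a proportion of patients. Adding 15 points gives 0.52, and both figures then enter as p1 and p2.

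**2. Reproducing 276.** Pooled two-proportion formula, 1:1 allocation:

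n per arm = [z_α √(2p̄(1−p̄)) + z_β √(p1(1−p1) + p2(1−p2))]² / (p2−p1)²

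With p1 = 0.37, p2 = 0.52 and p̄ = 0.445, the two square roots are 0.7028 and 0.6948, and z_β = 0.8416.

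- One-sided 5 %: [(1.645 × 0.7028 + 0.8416 × 0.6948)/0.15]² = 134.7, so 135 per arm, 270 in total. This is within about 2 % of 276. Power at 138 per arm is 0.81.
- Two-sided 5 %: [(1.960 × 0.7028 + 0.8416 × 0.6948)/0.15]² = 171.1, so 172 per arm, 344 in total. Power at 138 per arm is 0.71.

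So 276 is approached with a two-proportion calculation at one-sided 5 %, a level the article does not state. The mismatch below does not depend on this.

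**3. The powered quantity against what will be tested.**

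| | Power calculation | Primary endpoint 1 | Primary endpoint 2 | NOR-SASS C |
|---|---|---|---|---|
| Outcome | Relative fall in mean NIHSS | NIHSS 0 or fall ≥4 (yes/no) | mRS 0–1 (yes/no) | Clinical effect, superiority |
| Time | Day 7 in the reference data; none for the target | 24 h | 90 days | Not given for sizing |
| Patients | Thrombolysed | All NOR-SASS | All NOR-SASS | Not eligible for thrombolysis |
| Control rate given | 0.37, from a mean | None | None | None |
| Target difference given | 0.15 | None | None | None |

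**4. What 276 patients can show on a binary endpoint.** The documents give no control rates for the primary endpoints, so 40–60 % is an assumption, as are two-sided 5 % and all 276 patients in the comparison (138 per arm).

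Power = Φ{[|p2−p1| √n − z_α √(2p̄(1−p̄))] / √(p1(1−p1) + p2(1−p2))}

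Example at 0.40 against 0.55: (0.15 × √138 − 1.960 × 0.7062)/0.6982 = (1.762 − 1.384)/0.6982 = 0.541, so power is 0.71.

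| Control rate (assumed) | Power for +15 points | Detectable difference at 80 % power | Total needed for +15 points at 80 % |
|---|---|---|---|
| 0.40 | 0.71 | 16.8 points | 346 |
| 0.50 | 0.71 | 16.6 points | 340 |
| 0.60 | 0.76 | 15.7 points | 304 |

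At one-sided 5 % (z_α = 1.645) the same formula gives 0.81, 0.81 and 0.85 for +15 points. The answer therefore turns on a level that the article leaves open.

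**5. NOR-SASS C.** No number of patients, rate or effect is given, so no power can be computed from the document.

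**The case against.** Four points can be made on the other side.

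- **The target has no time point.** Day 7 belongs to the registry data, and the target may have been meant for 24 h. The target also draws on a meta-analysis and mild-stroke series that the article does not tabulate. This stands as far as it goes: a reader might infer that the trial was powered for day-7 NIHSS as such, and the text does not say that. But it does not name 24 h either, a mean reduction is still not the responder outcome, and the reading does nothing for mRS 0–1.
- **The calculation is for two proportions, and both primary endpoints are binary.** Under the assumptions above, 276 patients detect about 16–17 points, not far from the planned 15. This also stands. A reader might infer that the trial has no sample-size basis at all, and that is too strong. What is missing is a reason to expect about 15 points on these endpoints, and their control rates.
- **The 276 are attached to the thrombolysis comparison.** That is the more natural reading. A reader might infer that NOR-SASS C patients use up part of the 276 and leave A and B short. The document neither says this nor gives a share for C, so no loss of power can be put on it. Equally, it does not say that the 276 exclude C.
- **The analysis plan will settle the method.** "The exact method of the final analysis will be specified in the Statistical Analysis Plan" defers the analysis. The article does give a sample-size justification, and the fault lies in what that justification is tied to.

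**Conclusion.** The point holds in this form: the article's only power statement is not linked to either primary endpoint and does not cover the NOR-SASS C superiority hypothesis, so power of 0.8 is not shown for any primary comparison. This follows from the text and needs no assumption.

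The size is illustrative. With assumed control rates of 40–60 %, an assumed two-sided 5 % level and 138 per arm, the detectable difference at 80 % power is about 16–17 points and a 15-point difference has 71–76 % power. At one-sided 5 % a 15-point difference would reach 80 %. The shortfall is thus modest if 15 points is a realistic effect on these endpoints, which the article does not argue.

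A reader might go on to infer that NOR-SASS C has to be relabelled exploratory. The documents do not settle that. The Discussion calls sonothrombolysis with any thrombolytic the main aim, and marks only the tenecteplase part as probably too small for definite effect results. What they do establish is that C carries a superiority hypothesis to which the stated power does not apply.

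**What to change.** Keep the sample size. Then:

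1. Replace the power statement with the power, or the detectable difference, at that size for each of the two primary endpoints: the 24-h responder outcome and mRS 0–1 at 90 days. Take control rates for those endpoints from the NORSTROKE registry, and state alpha and sidedness.
2. Say whether the 276 include NOR-SASS C patients.
3. State that the power figure applies to the thrombolysis comparison (NOR-SASS A and B) and not to C. Unless a separate size is justified for C, its result should be read as an estimate with a 95 % confidence interval.

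The work is one registry tabulation, a short recalculation and revised wording. Recruitment targets do not change. The downside is that the stated power will probably look less favourable than 0.8, and that C is openly shown to have no power claim behind it unless one is added.
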